## Methods/design

### Study design

VINCI-AD is a single-site, single-blind, sham-controlled crossover pilot study in patients with amnestic MCI. Each participant is assessed at baseline (no stimulation) followed by randomisation to both sham stimulation and active tVNS stimulation over two subsequent study visits. The study comprises a baseline assessment (visit 1) followed 7–10 days later by either an active or sham stimulation study visit and again 7–10 days later by a third visit wherein the final condition (active or sham) will be undertaken. The inclusion of a sham stimulation condition is to confound for potential unblinding, which is common in device trials. Participants will be enrolled and consented by study clinician (HD). Please see Fig. 1 for an illustration of randomisation and sham stimulation technique.

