### Pre-specified exploratory analysis

#### Potential effects of acute tVNS on cognitive performance

VINCI-AD is a safety and feasibility study of tVNS device use in individual with MCI. Exploratory secondary analysis will also assess the potential benefits of acute tVNS on cognitive performance. Cognitive function will be assessed under identical conditions in all participants at all three visits and will encompass assessment of the following:

Face Name Association Task (FNAT): A cross-modal associative memory test [45, 46] hosted on E-PRIME (Psychology Software Tools, Sharpsburg, USA). The participant is shown 30 face-name pairs. After a brief interlude (less than one minute) participants are then shown a combination of faces, some of which have already been displayed. The assessment involves both accurate recognition of recently displayed faces and correct recall of associated names. tVNS has been shown to boost associative memory as assessed by this task in CU older adults [47] but has not been assessed in those with MCI.Sustained Attention to Response Task (SART): A computer based response inhibition task [48] hosted on E-PRIME (Psychology Software Tools, Sharpsburg, USA) This is similar to Go/No-Go or Stop/Signal tasks whereby participants are required to withhold response to a single, infrequent target (the digit 3) presented amongst a background of frequent non-targets (0–2, 4–9) to which the participant does respond by pressing the space key on the computer keyboard.SeaHero Quest ™ the electronic tablet-based app Sea Hero Quest (GLITCHERS © London, UK; University College London, London, UK) will be used whereby participants will be asked to complete 5 levels of increasing complexity of a nautical-themed navigation task designed to assess speed and accuracy of navigating a boat to a map target [49, 50].Language assessments will include list learning, semantic fluency, list recall and list recognition assessments adapted from RBANS battery as tVNS has demonstrated benefits in these domains in both healthy [26, 51] and clinical populations [11, 12].Working memory will be assessed via digit span forward and backward which will be undertaken as part of the adapted RBANS battery.

Participants will wear the portable NIRS analysis device during all cognitive tasks so that the TSI may be measured continuously during cognitive tasks at baseline, during active and during sham stimulation.

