#### Potential effects of acute tVNS on inflammatory markers

Aseptic peripheral venepuncture will be performed 50–60 min following neurocardiovascular and cognitive assessments have been undertaken at all three study visits. 7-10ml of blood will be taken in EDTA Vaccutainers, centrifuged at 3,400 rpm for 10 min at 18 °C and supernatant stored in 1ml aliquots at -80 °C for later analysis. A custom-battery of 12 cytokines and chemokines will be analysed using the MesoScale Discovery (MSD) V-PLEX Electrochemoluminescence assay according to standard protocols and includes: IL-1RA, IL-6, IL-8, IL-10, IL-17 A, MIP-1 β, IL12p70, IP-10, TNF- α, MCP-1, Eotaxin, IFN- γ based on known associations with MCI in international literature [53, 54]. Please see Fig. 2 for study visit schedules including minutes of stimulation, methods of assessment and timelines.

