### Sample size

To establish the safety and feasibility of tVNS in a population of older adults with MCI, VINCI-AD aims to recruit 40 participants for inclusion. This sample size is based on previous literature which investigated the effects of tVNS in healthy young adults [19–21, 23, 55] and also CU older adults [47]. Potential effect sizes from the results of this feasibility study will inform an accurate power calculation for future definitive trials.

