### Statistical analysis

VINCI-AD will assess the safety and feasibility of tVNS in older adults with MCI. All participants will be included in final analysis in an “intention-to-treat” fashion. Statistical analysis will be conducted using MATLAB (The MathWorks, Inc., Natick, MA, USA), SPSS (IBM SPSS Statistics for Windows, Armonk, NY: IBM Corp) and GraphPad Prism (GraphPad Software, Inc., San Diego, CA, USA). We anticipate that TSI analysis will require cleaning to remove “noisy” channels i.e. removing large spikes (changes in oxy-Hb larger than 0.5 mM/mm in amplitude); noisy channels will be excluded from analyses and data analyses will utilise software Platform for Optical Topography Analysis Tools [56] with a bandpass filter with cut-off frequencies of 0.01–0.8 Hz to remove instrumental or physiological noise [57].

In the first instance, descriptive statistics will be described for the cohort, reported as means (with standard deviations) or medians (with inter-quartile ranges) and proportions (percentages) as appropriate.

The primary aim of the current study is to assess the safety and feasibility of tVNS in MCI. To assess safety, a chi-square test will compare the number of adverse events reported during the active vs. sham condition. Further safety assessment will elicit symptoms experienced during active stand (using a chi-square statistic), peripheral (beat-to-beat blood pressure response to orthostasis – using mixed-effects linear regression with study condition as the independent variable, with random intercepts for study participant) and central (TSI – also assessed using a linear mixed-effects model). Feasibility will be reported via recruitment rates, successful enrolment, and study completion in proportions and percentages. Tolerability will be assessed using Likert scales, which will be compared between active and sham conditions using paired between-condition statistics (t-test if normally distributed or non-parametric equivalent). Descriptive statistics will be used to report acceptability using the modified Kettle test.

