Exploratory secondary aims of this study (cognitive testing, HRV analysis, inflammatory responses) will be analysed using a repeated three – way analysis of variance (ANOVA) if parametric or Kruskal-Wallis test if non-parametric analysis required, with Bonferroni corrections for multiple comparisons. We will explore the effects of concentrations of pro-inflammatory plasma cytokines on cognitive and neurocardiovascular characteristics. Missing data will be handled by applicable statistical methods including multiple imputation.

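### The non-parametric fallback for the exploratory outcomes, Kruskal-Wallis, ignores that the three conditions are measured in the same participants, and the three-way label on the ANOVA does not fit the design

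*Protocol article*

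**What the plan says.** The Study design section sets out a within-participant comparison: "Each participant is assessed at baseline (no stimulation) followed by randomisation to both sham stimulation and active tVNS stimulation over two subsequent study visits". The exploratory outcomes follow that layout. For cognition, "Cognitive function will be assessed under identical conditions in all participants at all three visits". Blood for cytokines is drawn 50 to 60 minutes "following neurocardiovascular and cognitive assessments have been undertaken at all three study visits". Table 1 schedules heart rate variability at all three visits as well.

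The Statistical analysis section says that these outcomes "will be analysed using a repeated three – way analysis of variance (ANOVA", and continues "if parametric or Kruskal-Wallis test if non-parametric analysis required", with Bonferroni correction. It names no three factors.

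The same section respects the pairing elsewhere. Tolerability scores are compared between active and sham with a paired t-test or its non-parametric equivalent. Blood pressure on standing is analysed by a mixed model with a random intercept for each participant.

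**The concern.** Kruskal-Wallis is a test for independent groups. Applied here, it treats the three values of each of 40 people as if they came from 120 different people. Differences between people then stay in the yardstick against which the condition effect is judged, although the crossover was designed to remove them. The matching rank test for three conditions in the same people is Friedman.

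The two branches of one rule therefore disagree. If a variable is judged parametric, its pairing is used; if not, its pairing is ignored. RMSSD and the 12 cytokines are plausible candidates for the second branch, though the article gives no distributional information.

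The three-way label is a separate and smaller matter. The design has one within-person condition factor with three levels, which is a one-way repeated-measures layout.

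At stake is a signal missed in the exploratory results, which the article intends as a guide to later trials.

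**Working it through.** **No figure to reproduce.** The article states no alpha, power, effect size, standard deviation or within-person correlation for these outcomes. On size it says "VINCI-AD aims to recruit 40 participants for inclusion" and "This sample size is based on previous literature which investigated the effects of tVNS in healthy young adults". Only n = 40 and the three conditions come from the document. Assumed: two-sided alpha 0.05 before any Bonferroni correction, no dropout, total SD 1, equal correlation ρ between any two conditions, and a shift of d SD in one condition.

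**Step 1: false-positive rate by formula.** The difference between two condition means in the same people has variance 2(1−ρ)/n. An independent-groups test assumes 2/n. With no effect, the Kruskal-Wallis statistic therefore behaves approximately as (1−ρ) times a chi-square on 2 degrees of freedom. Its 5% cut-off is 5.991, so the true rate is about exp(−5.991 / (2(1−ρ))):

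- ρ = 0.3: exp(−4.28) = 1.4%
- ρ = 0.5: exp(−5.99) = 0.25%
- ρ = 0.7: exp(−9.99) = 0.005%

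**Step 2: simulation, n = 40, normal data, nominal 5%, d = 0.4.**

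| ρ | True alpha, Kruskal-Wallis | Power, Kruskal-Wallis | Power, Friedman | Power, one-way repeated-measures ANOVA |
|---|---|---|---|---|
| 0 | about 5% | 44% | 34% | 43% |
| 0.3 | 1.8% | 37% | 44% | 57% |
| 0.5 | 0.2% | 32% | 59% | 74% |
| 0.7 | about 0% | 26% | 80% | 93% |

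The ANOVA column comes from a repeat run of 4,000 trials per setting. That run gave 41/36/33/27% for Kruskal-Wallis and 32/43/58/81% for Friedman at the four correlations, so the rank-test figures are stable to about 3 points. Friedman held its level, at 4.7% to 5.7%.

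**Step 3: other effect sizes (2,000 trials per setting), Kruskal-Wallis against Friedman.**

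- d = 0.3: 18% against 27% (ρ = 0.3), 14% against 36% (0.5), 7% against 54% (0.7)
- d = 0.5: 59% against 62% (ρ = 0.3), 56% against 78% (0.5), 57% against 95% (0.7)
- ρ = 0, d = 0.5: 59% against 48%, so Kruskal-Wallis is ahead

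Log-normal data gave nearly the same figures. This is expected: both tests use ranks only, so exponentiating the data leaves them unchanged. The comparison therefore also covers skewed data, where the fallback would apply.

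**Step 4: cross-check on active against sham alone, d = 0.5.** Paired power is Φ(d√40 / √(2(1−ρ)) − 1.96); the unpaired figure sets ρ = 0.

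- Unpaired: Φ(3.162/1.414 − 1.96) = Φ(0.28) = 61%
- Paired, ρ = 0.5: Φ(3.162/1 − 1.96) = Φ(1.20) = 88%
- Paired, ρ = 0.7: Φ(3.162/0.775 − 1.96) = Φ(2.12) = 98%

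The direction and rough size of the loss agree with the simulation.

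**The case against.** The strongest reply is that these outcomes are exploratory, the primary safety and feasibility analyses do not use this test, and the error is conservative, so it creates no false claim of benefit. All of that stands and limits the weight of the point. It does not make the test suitable. Nor can the matter be left to an analysis plan that is not shown, because the article names the test.

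Four stronger readings are tempting, and the document does not support them.

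- **That most of the crossover's power is lost.** Over the values tried, the loss runs from none at zero correlation to most of the power at high correlation with a small effect. The article gives neither the correlation nor the effect size.
- **That the three-way label also costs power.** The ANOVA is still described as repeated, so the within-person structure is kept. The label needs correcting, but the loss arises only in the fallback.
- **That repeated-measures ANOVA drops people with a missing visit, against the statement** "All participants will be included in final analysis"**.** The same section provides for multiple imputation, so no such conflict is shown. Friedman too needs all three values.
- **That effect sizes for the next trial would be wrong.** The article does not say they will be taken from the Kruskal-Wallis statistic. The choice of overall test leaves mean differences and standard deviations unchanged.

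**Conclusion.** The point holds as a should-fix of moderate weight. The named fallback is wrong for three measurements on the same people and is inconsistent with the paired methods elsewhere in the same section. At an assumed 0.4 SD shift in one condition, Friedman gains about 7, 27 and 54 percentage points over Kruskal-Wallis at within-person correlations of 0.3, 0.5 and 0.7, and nothing at zero. These figures rest on 40 complete participants, equal correlations between conditions and an uncorrected 5% level. They illustrate the range and are not estimates for this trial. How many outcomes would take the fallback is unknown.

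**What to change.** In the Statistical analysis section:

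1. Replace Kruskal-Wallis with the Friedman test, followed by Bonferroni-corrected Wilcoxon signed-rank tests for the pairwise contrasts, including active against sham. Alternatively, use the mixed model with a participant random intercept, already planned for blood pressure, on suitably transformed data.
2. Replace three-way with one-way repeated measures on a condition factor with three levels (baseline, active, sham).

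The cost is about two lines of text. SPSS and GraphPad Prism, both already named, can run these analyses. Recruitment, visits and data collection do not change. The correction should be made before the exploratory data are analysed.

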### Data collection and data management

Data will be collected by research personnel, all of which have been trained in the principles of good clinical practice. Experimental data is pseudo-anonymised then recorded and managed on a secure encrypted local database. Filled-out data collection files will be transferred to the secure database by one researcher. Digitalised data are stored for 5 years after study end. For each participant, a physical Case Report Form, containing all physical source material, will be kept in a secure and locked location for 5 years. Serum samples will be stored at the research laboratory for a maximum of 5 years. Samples will be anonymised and labelled with subject randomisation ID and date of sample collection.

## Discussion

There are limited published studies investigating the efficacy of tVNS in cognition [58] and notably assessments of neurocardiovascular safety of device treatment in this population are lacking. This study investigates the safety and feasibility of a novel handheld neural stimulation device in an older population with memory impairment. Older adults with mild memory impairment are often not included in clinical or device trials [59] despite evidence that older adults with chronic conditions are willing and capable of engaging in digital self-management, and that this cohort can develop and master the technical skills necessary to do this [60]. To our knowledge no formal studies into the safety and tolerability of these devices in a population with cognitive diagnoses has been completed, and most trial designs have not included both baseline and active/sham stimulation arms to control for unblinding bias for the condition. According to findings from a meta-analysis that synthesised all reported adverse events, the safety profile of non-invasive vagal stimulation is excellent [42].

This study has the following strengths. Participants undergo repeated assessments at three time points which will support reliable inference of any effects at statistical analysis. There is also no age limit on this study’s eligibility criteria which is important, as upper age limits in particular have historically excluded older adults from many interventional trials thus limiting generalisability of results. Limitations of this study include planned recruitment of participants from a clinical population to repeated assessments in a clinical research setting which may be challenging in an older cohort with other medical or lifestyle commitments.

In this pilot intervention study we aim to generate clinical, digital and laboratory data to assess to safety, tolerability and potential efficacy for tVNS in a population with amnestic MCI. Further outcomes will include metrics to design future definitive intervention studies, and explore the associations between vagally-mediated neurocardiovascular, inflammatory and cognitive function in this population.

## Data Availability

Not applicable. Data will be pseudo-anonymised using participant unique identification codes assigned at study enrolment and entered to a secure data system on locally-hosted servers for analysis. HD and SK will have access to the secured trial dataset. Data will be published in relevant peer-reviewed journals.
